### Sample size and power calculations

Power calculations for all TB/HIV patients were based on our primary outcomes ART initiation and TB treatment success. Based on previous programmatic data, we anticipated an average of 100 newly registered TB/HIV patients at each of the 12 study clinics over the first 24 months of observation. When the study was designed, available data demonstrated that only 27% of HIV-infected TB patients in Lesotho had received ART, and the TB treatment success rate was 70% for new smear positive cases, 64% for new smear negative and extrapulmonary cases, and 62% for retreatment cases (HIV-positive and HIV-negative cases combined) (42). Assuming a two-sided Farrington & Manning Likelihood Score Test with *α*=0.05 and an intra-cluster correlation coefficient (ICC) of 0.05, we will have 83% power to detect a difference in ART initiation from 40% (SOC) to 60% (CIP), and 91% power to detect a difference in TB treatment success from 65% (SOC) to 85% (CIP) (PASS 2008, NCSS Statistic Software). As per standard practice, patients who die or are lost to follow-up before ART initiation or TB treatment completion are considered to have not initiated ART or to have not achieved TB treatment success, respectively, and thus power calculations for these outcomes do not include an allowance for attrition.

Power calculations for measurement cohort participants were based on our primary outcome ART retention. Assuming 100 TB/HIV patients in each of the 12 study clinics, 40% ART initiation at SOC clinics, and at least 80% study enrollment, we aimed to enroll 384 participants (32 per clinic) initiating ART in the measurement cohort. Assuming a two-sided Farrington & Manning Likelihood Score Test with *α*=0.05 and ICC of 0.05, we will have 87% power to detect a difference in ART retention from 70% (SOC) to 90% (CIP).

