## Methods/design

The START Study is a two-arm, mixed-methods, cluster-randomized trial. Twelve health facilities with integrated TB/HIV clinics (the clusters) were randomized to deliver a CIP or standard of care (SOC), following stratification by facility type (hospital or health center).

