### Facility selection

Twelve of 17 public health facilities in Berea District were selected for participation. The remaining five health facilities were excluded from the sampling frame because patient volume was very low (on average, fewer than six TB patients notified per quarter). Both hospitals (*N*=2) and health centers (*N*=10) were included to enhance generalizability. A single district was chosen in collaboration with MOH to enhance internal validity by ensuring comparability of health facilities randomized to either study arm, and maximize cost efficiency.

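### The stated powers of 83%, 91% and 87% use a large-sample normal reference although only about 10 between-site degrees of freedom exist; at a true 5% level they are about 74%, 86% and 81%.

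*Protocol article*

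**What the plan says.** Under Methods/design, the article says "Twelve health facilities with integrated TB/HIV clinics (the clusters) were randomized to deliver a CIP or standard of care (SOC", after stratification by facility type. Facility selection gives the strata: 2 hospitals and 10 health centers.

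Under Sample size and power calculations:

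- Size for the two outcomes measured on all patients: "we anticipated an average of 100 newly registered TB/HIV patients at each of the 12 study clinics over the first 24 months of observation".
- Size for the retention outcome: "we aimed to enroll 384 participants (32 per clinic) initiating ART in the measurement cohort".
- Test: a two-sided Farrington and Manning likelihood score test, alpha 0.05, ICC 0.05, computed in PASS 2008.
- Results: "we will have 83% power to detect a difference in ART initiation from 40% (SOC) to 60% (CIP"; "91% power to detect a difference in TB treatment success from 65% (SOC) to 85% (CIP"; "87% power to detect a difference in ART retention from 70% (SOC) to 90% (CIP".

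The Data analysis section plans a generalized linear mixed model with a random intercept for site. It lists fixed effects for study condition and patient characteristics. It mentions neither a facility-type term nor a degrees-of-freedom method.

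**The concern.** Arm is assigned to facilities, so the arm contrast is a comparison of 6 sites with 6 sites. The between-site variance has to be estimated from those same 12 sites. A design effect inflates the variance for the correlation, but it does not allow for how poorly that variance is known when there are few sites. Using 1.96 treats it as known.

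If the final test uses a small-sample reference, its power is below the printed figures. If it uses a normal reference, its type I error is above 5%. In neither case are the printed level and power both true.

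The main consequence is for a null result on ART initiation, the first primary outcome listed. It would be read against a stated 17% chance of missing the planned effect (100 − 83), when at a true 5% level that chance is about 26% (100 − 74).

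**Working it through.** **Inputs.** All come from the article except the 6:6 split, which is inferred from 12 sites in two arms.

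- k = 6 sites per arm
- m = 100 patients per site (ART initiation, TB success) or 32 (retention)
- ICC = 0.05, two-sided alpha = 0.05
- Rates 40% v 60%, 65% v 85%, 70% v 90%

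**Step 1: design effect and effective size per arm.** DE = 1 + (m − 1) × ICC; effective n = k × m / DE.

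- m = 100: DE = 1 + 99 × 0.05 = 5.95; n = 600 / 5.95 = 100.8
- m = 32: DE = 1 + 31 × 0.05 = 2.55; n = 192 / 2.55 = 75.3

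**Step 2: standardised difference.** d = (p2 − p1) / √{[p1(1 − p1) + p2(1 − p2)] / n}.

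- ART initiation: 0.20 / √(0.48 / 100.8) = 2.90
- TB success: 0.20 / √(0.355 / 100.8) = 3.37
- Retention: 0.20 / √(0.30 / 75.3) = 3.17

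**Step 3: reproduce the stated figures.** With a normal reference, power is Φ(d − 1.96) (unpooled variance), or the version with pooled variance under the null. **Step 4: replace the normal by t.** With 12 sites and two arm means, df = 12 − 2 = 10 and the critical value is 2.228 instead of 1.96. Power is the upper tail of the noncentral t with noncentrality d.

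| Outcome | Stated | Normal, pooled to unpooled | t, 10 df | Simulated, t with 10 df |
|---|---|---|---|---|
| ART initiation | 83% | 81.6–82.6% | 74.3% | 73.4% |
| TB treatment success | 91% | 91.3–92.1% | 85.9% | 85.5% |
| ART retention | 87% | 87.4–88.7% | 81.4% | 81.7% |

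The stated figures are matched within about 2 points by the normal calculation and not by the t calculation, so the large-sample reference is what was used.

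The simulation drew 200,000 beta-binomial trials per scenario and applied a t test to the site proportions.

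**Step 5: true size of the normal cut-off.** For t with 10 df, 2 × P(T > 1.96) = 0.078. Simulating under no effect gave 7.7–7.8% with the 1.96 cut-off and about 5% with the 10-df cut-off.

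**Step 6: variant with a facility-type term.** One more degree of freedom is spent, so df = 9 (critical value 2.262). Power is 73.3%, 85.0% and 80.5%, before crediting any between-site variance that the term removes.

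**Step 7: detectable difference.** Solving the 10-df calculation for 80% power from a control rate of 40%, with m = 100, gives an intervention rate of 61.4%, a difference of 21.4 points against the planned 20.

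**The case against.** **The calculation does use the 12 clusters.** This stands. Site number and ICC enter through the design effect, and under the named score test the figures are computed correctly to within about 2 points. A reader might infer that clustering was ignored or the arithmetic is wrong; the article supports neither. What is missing is the allowance for few degrees of freedom.

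**The effect is modest.** This stands in part. TB success and retention stay above 80%, and the detectable ART-initiation difference moves by only 1.4 points. An ICC of about 0.038 instead of 0.05 would restore 83% with 10 df. But the article fixes the ICC at 0.05 and prints the power as a result of it.

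**The analysis may be properly calibrated.** This stands. The degrees-of-freedom method is commonly left to an analysis plan, which is not shown. Nothing here shows that the trial's own test will have an inflated error rate; the point concerns the printed powers.

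**Power could be lower still.** A reader might infer this from two features, and neither yields a firm figure.

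- The 9-df results assume a facility-type term that the Data analysis section does not list, and such a term could also reduce between-site variance and recover power.
- Site sizes probably differ, since 100 is an average over hospitals and health centers, and sites were left out for having "fewer than six TB patients notified per quarter". That rule describes the excluded sites; it does not show that any included site lies near the floor. The article gives no site sizes, so any numerical loss from imbalance rests on assumed sizes. Figures that weight sites by patient count would also describe an analysis other than the planned mixed model.

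**Recruitment and follow-up are complete.** True, so restating power changes no design feature. It does change the yardstick the article offers for a null result.

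**Conclusion.** The point holds in this form: the three powers are design-effect calculations with a normal reference, and they overstate what 12 sites provide at a true two-sided 5% level. The overstatement is about 9 points for ART initiation (83% to 74%), 5 for TB treatment success (91% to 86%) and 6 for retention (87% to 81%). Only ART initiation drops below 80%.

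This rests on 6 sites per arm, equal site sizes, the article's ICC of 0.05 and its planned rates. Unequal sizes would lower power further, by an amount the article does not allow one to calculate.

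**What to change.** In Sample size and power calculations:

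1. Restate the powers on a t reference with 10 degrees of freedom: about 74%, 86% and 81%. If a facility-type term is to be fitted, give the 9-df values instead (about 73%, 85% and 80%), noting that they precede any variance the term removes.
2. Add the ART-initiation difference detectable with 80% power on the 10-df basis: about 21.4 points (40% against 61.4%).
3. State the 6:6 split and the equal-size assumption, and say that unequal sizes would reduce power. Label any unequal-size example as an assumption unless actual site sizes are used.

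The cost is text only. No data, design or analysis step changes, but the stated figures become less favourable.

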### Data analysis

An intent-to-treat analysis will be used. In addition, when measuring adherence in the measurement cohort, an as-treated analysis will be used to exclude participants who died or discontinued medications due to adverse events. Generalized linear mixed models (Proc Glimmix procedures in SAS v9.3 with a random intercept for study site) will be applied to test for a difference between study arms for dichotomous (ART initiation, ART retention, TB treatment success, sputum smear conversion) and continuous (ART adherence, change in CD4+ count, TB treatment adherence) outcomes; frailty models (Proc Phreg procedures in SAS v9.3 with random intercept for study site) will be utilized for time to event analysis (time to ART initiation) to account for the clustering of characteristics that may occur among patients attending the same study site. These approaches will provide appropriate adjustments to the standard errors accounting for potential non-independence of observations (43). Models will include fixed effects for study condition, patient characteristics, time-varying adherence measures and CD4+ count (for change in CD4+ count) and random effects for site. Participants who transferred to another site before ART initiation will be censored, and death before ART initiation will be treated as a competing risk.

For the cost-effectiveness analysis, a model will be created to estimate the incremental cost of CIP relative to SOC. The costs will be composed primarily of the variable costs involved in training nurses and convening VHW, but will also include the costs of administering SMS messages and the fixed costs involved in administering the intervention. The incremental cost-effectiveness of CIP will be estimated as the ratio of the incremental costs to incremental effectiveness with effectiveness measured in terms of the study's primary outcomes.

For analysis of acceptability of the CIP, two investigators will independently review the first five interviews from each group of key informants to develop a preliminary checklist of codes using a grounded theory framework (41, 44). The individual checklists will be compared and reconciled to create a coding dictionary, which will be used by the study team to independently code each interview. Additional codes will be added if they emerge in the analysis of subsequent interviews. Codes will accordingly serve as building blocks for qualitative concepts and themes. Themes will be cross-checked to enhance inter-rater reliability, and negative case analysis and critical reflexivity will be used to strengthen analytic credibility (41, 45). Data from patients and providers will be analyzed separately and comparatively. Data analysis will explore contextual factors related to the acceptability of CIP components among patients; detect differences, if any, between men and women; and will shed light on common and divergent characteristics of patients’ and providers’ barriers and facilitators.

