#### Programmatic components of CIP: nurse training and mentorship in TB/HIV co-treatment, using a clinical algorithm

All nurses working in CIP clinics participated in a 2-day training on the scientific evidence and guidelines regarding treatment of TB/HIV co-infection, the importance of early ART initiation during TB treatment to improve survival, and use of a clinical algorithm to manage TB/HIV patients. Job aids, such as laminated desk charts and posters depicting the algorithm, were provided for each consultation room to support intervention delivery. Clinic nurses used the algorithm to initiate ART; monitor for adherence, treatment response, and side effects; and diagnose and manage adverse events, including immune reconstitution inflammatory syndrome (IRIS). Nurses explained to TB/HIV patients that ART can improve survival, encouraged ART initiation, and referred patients to the facility-based lead village health worker (LVHW) for further education. Nurses also delivered specific adherence messages and assessed ART and TB treatment adherence at follow-up visits, referring patients to the LVHW for additional adherence counseling. A nurse program monitor visited the clinics two to three times per month to provide ongoing mentorship in TB/HIV co-treatment to the clinic nurses and LVHW and provided refresher training as needed.

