#### Psychosocial components of CIP

Psychosocial components of CIP were delivered by VHW, whose role encompassed social support, system navigation, referrals, and advocacy. VHW responsibilities included providing information; communicating with patients; encouraging ART initiation, adherence to ART and TB treatment, and retention in care; offering support and empathy; providing referrals; and advocating for patients. In order to improve VHW oversight and coordination, one to two VHW were assigned to be LVHW at each facility, according to patient volume. LVHW were chosen by a joint committee of their peers and the nurse in charge, and received a monthly stipend of 750 loti (approximately 70.0 USD). All VHW completed a 4-day training in both didactic learning and interactive techniques, including case studies and role-playing to develop skills. LVHW completed an additional 2 days of training on their additional responsibilities at the health facility, as well as their role supervising VHW in the community.

LVHW assigned new TB/HIV patients initiating ART to a community-based VHW, who provided adherence support between clinic visits. VHW conducted home visits and contacted patients by phone, weekly for the duration of TB treatment, to discuss adherence and side effects. They also followed up with patients who missed clinic appointments, contacting the LVHW or nurse for guidance when necessary, and linked patients with community-based services as needed. VHW were provided with airtime vouchers (40 loti, approximately 3.7 USD) each month.

LVHW used a TB/HIV treatment literacy curriculum to provide group health education sessions at the health facility. They also met individually with TB/HIV patients and their treatment supporters to provide ART preparation and adherence counseling for the duration of their TB treatment. A scripted, illustrated flipchart was developed for LVHW. It provides information on the natural history of HIV, importance of early ART initiation, use of TB and antiretroviral medications, common side effects, and the importance of adherence. In response to an expressed need from LVHW, a second flipchart that provides information on and support for HIV disclosure was also developed.

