#### Measurement cohort

In addition, a measurement cohort of TB/HIV patients initiating ART was recruited. Inclusion criteria were 1) HIV-infected; 2) on TB treatment; 3) initiated ART within 2 months of TB treatment initiation; 4) aged 18 or older; 5) English- or Sesotho-speaking; and 6) capable of and willing to provide informed consent within 3 working days of ART initiation. Patients with multidrug-resistant TB were excluded from the measurement cohort.

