### Primary and secondary endpoints

Primary outcomes include: 1) ART initiation, 2) ART retention, and 3) TB treatment success. Secondary outcomes include: 1) time to ART initiation, 2) ART adherence, 3) change in CD4+ count, 4) sputum smear conversion, 5) TB treatment adherence, 6) cost-effectiveness, and 7) acceptability. All outcomes pertain to the individual participant level. ART initiation is defined as the percentage of TB/HIV patients newly registered during the period of observation who initiated ART during TB treatment, based on review of clinic records. ART retention is defined as the percentage of measurement cohort participants who attended their 6-month clinic visit (within a 1-month window) and reported ART use. Deaths and transfers will be considered not retained. TB treatment success is defined as the percentage of TB/HIV patients whose TB treatment outcome is documented in the TB register or treatment card as treatment completion or cure, as defined by the WHO (40). Time to ART initiation will be expressed as the number of days from TB treatment initiation to ART initiation. Adherence is determined separately for ART and TB treatment and defined by the percentage of total prescribed doses ingested, averaged across medicines for each month of treatment, from the unannounced pill counts. Change in CD4+ count is defined as the difference in CD4+ count 6 months after TB treatment initiation. Sputum smear conversion is defined as the percentage of smear positive pulmonary TB cases that converted to smear negative after 8 weeks of treatment (40). Incremental cost-effectiveness will be estimated as the ratio of the incremental costs of the CIP per ART initiation, retention, and TB treatment success. Acceptability of intervention components will be characterized via in-depth qualitative analysis and interpretation (41). Table 2 lists the study outcomes for each group of participants.

**Table 2 T0002:** Study outcomes

Study outcome	All TB/HIV patients	Measurement cohort	Key informants – ART early initiators	Key informants – ART non/late initiators	Key informants-health care workers
ART initiation^a^	X				
ART retention^a^		X			
TB treatment success^a^	X				
Time to ART initiation	X				
ART adherence		X			
Change in CD4+ count		X			
TB treatment adherence		X			
Sputum smear conversion	X				
Incremental cost-effectiveness		X			
Acceptability of intervention components			X	X	X
Reasons for ART non/late initiation				X	

a Primary outcomes.

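### The added 'as-treated' adherence analysis drops whole participants for post-allocation events that the package may affect, and loses their valid earlier pill counts

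*Protocol article*

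**What the plan says.** The Data analysis section sets the general principle: "An intent-to-treat analysis will be used". For adherence in the measurement cohort it then adds a further analysis: "an as-treated analysis will be used to exclude participants who died or discontinued medications due to adverse events". The unit removed is the participant, not the month.

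Under Primary and secondary endpoints, adherence is a secondary outcome, determined separately for ART and for TB treatment and "defined by the percentage of total prescribed doses ingested, averaged across medicines for each month of treatment, from the unannounced pill counts". The Data collection section says that these counts are made monthly by telephone throughout TB treatment.

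Other parts of the protocol handle deaths differently. For the primary retention outcome, "Deaths and transfers will be considered not retained". The sample size section counts patients who die before ART initiation or before completing TB treatment as failures on those two outcomes.

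**The concern.** Death and stopping for an adverse event both happen after clinics were allocated. If the package changes how often they happen, or how often a stop is attributed to an adverse event, the exclusion removes different kinds of patients from the two arms. The remaining contrast is then among survivors who tolerated treatment in each arm, and randomisation does not protect that comparison.

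Two further faults do not depend on event rates. The excluded participants may have given usable pill counts for the months before the event, and these are lost. And an as-treated analysis normally regroups people by treatment received; here nobody is regrouped, so a reader would misjudge what was estimated.

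At stake is the interpretation of a supplementary result on two secondary outcomes.

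**Working it through.** **1. Check of the cohort figures.** None of the plan's power figures uses adherence, but the retention calculation describes the same cohort and supplies the design effect used in step 4. Inputs from the sample size section: 384 participants, 32 per clinic, 12 clinics, ICC 0.05, two-sided alpha 0.05, 70% against 90%. Assumed: six clinics per arm, since the split is not stated.

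- Design effect = 1 + (32 - 1) x 0.05 = 2.55.
- Effective n per arm = 6 x 32 / 2.55 = 192 / 2.55 = 75.3.
- Standard error with pooled p = 0.80: sqrt(2 x 0.80 x 0.20 / 75.3) = 0.0652. Unpooled: sqrt((0.21 + 0.09) / 75.3) = 0.0631.
- z = (0.20 - 1.96 x 0.0652) / 0.0631 = 1.14, so power is 87.4%. The plan states 87%, which reproduces.

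**2. Can exclusion depend on arm?**

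- *Adverse events.* Table 1 gives the co-treatment algorithm to CIP clinics only. Their nurses use it to "diagnose and manage adverse events, including immune reconstitution inflammatory syndrome (IRIS"). Community health workers contact CIP patients "weekly for the duration of TB treatment, to discuss adherence and side effects".
- *Death.* CIP nurse training covers "the importance of early ART initiation during TB treatment to improve survival".
- *Attribution.* The assignment section says that participants, health care workers and study staff were not blinded.

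So exclusion can differ by arm. The protocol gives no rates to show that it does.

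**3. Size, on assumptions that are not in the documents.** Suppose that the package changes nobody's adherence and that both arms contain the same mix of patients. Mean adherence is 92% in those never at risk of removal and a in those who would be removed in at least one arm, with a from 60% to 80%. Let s and c be the shares removed in SOC and CIP.

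- If s > c, CIP keeps a group of size s - c that SOC drops. The spurious difference (CIP minus SOC) = -(92 - a) x (s - c) / (1 - c).
- If c > s, it is +(92 - a) x (c - s) / (1 - s).

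Example: s = 0.10, c = 0.05, a = 80 gives -12 x 0.05 / 0.95 = -0.63.

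| Removed SOC / CIP | a = 80 | a = 70 | a = 60 |
|---|---|---|---|
| 10% / 10% | 0.0 | 0.0 | 0.0 |
| 10% / 5% | -0.6 | -1.2 | -1.7 |
| 15% / 5% | -1.3 | -2.3 | -3.4 |
| 20% / 10% | -1.3 | -2.4 | -3.6 |
| 10% / 15% | +0.7 | +1.2 | +1.8 |

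**4. Scale.** With an assumed SD of 10 to 20 points, the standard error of the arm difference is SD x sqrt(2 / 75.3), or 1.6 to 3.3 points. In the less favourable rows the shift is of the same order as the standard error; in the milder rows it is well below it.

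**5. The alternative under the same assumptions.** If every participant stays in and contributes the mean of the months before the event, both arms keep the same mix and the spurious difference is zero.

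**The case against.** The strongest reply is that the analysis is supplementary. It stands beside an intent-to-treat analysis that excludes nobody on these grounds, and no primary outcome uses the exclusion. That is right, and it sets the weight of the point.

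A reader might infer that this rule destroys a comparability the arms otherwise had. The documents do not support that. Adherence is measured only in patients who "initiated ART within 2 months of TB treatment initiation" and who consented, by nurse referral in an unblinded trial. All of this comes after allocation, and ART initiation is itself a target of the package. The rule adds a second filter to a cohort already selected.

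A reader might also infer that removal is bound to differ by arm. That is not shown either. Everyone in this cohort started ART within the two-month window, so only timing inside it remains as a route from earlier ART to survival. SOC patients also have monthly monitoring of side effects, both arms complete the same questionnaires, and study staff were trained to assess for adverse events. Nor are death and adverse-event discontinuation named outcomes of the trial; the package may affect them, and no more can be said.

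Finally, pre-event months might be kept under a fuller plan that is not shown. But the stated wording excludes participants, and that wording is what should be corrected.

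**Conclusion.** The point holds as a minor one. The supplementary adherence analysis selects on post-allocation events that the package may affect, discards usable pill counts and carries the wrong label. This adds an arm-dependent selection risk to the ART and TB adherence contrasts.

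Its size and direction are unknown. The range in the working, from -3.6 to +1.8 points with zero under equal removal of similar patients, rests wholly on assumed removal shares and adherence levels. It shows what is possible and is not an estimate for this trial. The primary outcomes, the plan's power figures and the intent-to-treat adherence analysis do not change.

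**What to change.** In the Data analysis section, replace the exclusion as follows:

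- Keep all measurement-cohort participants in the supplementary analysis. Use their monthly pill counts up to death or discontinuation for an adverse event, and leave later months uncounted.
- Call it adherence while alive and on prescribed treatment, and drop the as-treated label.
- Report the number of deaths and adverse-event discontinuations by arm beside the result.
- State that the adherence conclusion rests on the intent-to-treat analysis.

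The cost is wording and analysis code. Monthly counts were part of the planned data collection, follow-up is complete, and the analysis is still described in the future tense.

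The limits should be stated. The result remains conditional on being alive and on treatment, and a participant with no count before the event contributes nothing. The zero in step 5 of the working also needs each participant's months to be averaged first; if months are pooled, participants with early events weigh less and part of the shift can return.

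### With 12 randomized sites, a random site intercept alone does not ensure a 5% test: on a large-sample reference, which the power figures imply, type I error is about 8–10% at ICC 0.05

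*Protocol article*

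**What the plan says.** The unit of randomization is the facility: "Twelve health facilities with integrated TB/HIV clinics (the clusters) were randomized" (Methods/design). Facility selection gives the strata: "Both hospitals (*N*=2) and health centers (*N*=10) were included to enhance generalizability". The number of sites per arm is not stated.

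Data analysis assigns dichotomous and continuous outcomes to "Proc Glimmix procedures in SAS v9.3 with a random intercept for study site", and time to ART initiation to "Proc Phreg procedures in SAS v9.3 with random intercept for study site". It then gives the assurance "These approaches will provide appropriate adjustments to the standard errors accounting for potential non-independence of observations". It names no estimation method (REML or maximum likelihood), reference distribution, denominator degrees of freedom or small-sample correction.

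Sample size and power calculations uses a two-sided score test at alpha 0.05 with ICC 0.05. On cluster size it says "we anticipated an average of 100 newly registered TB/HIV patients at each of the 12 study clinics over the first 24 months of observation" and "we aimed to enroll 384 participants (32 per clinic) initiating ART in the measurement cohort". Stated power is 83% for ART initiation (40% v 60%), 91% for TB treatment success (65% v 85%) and 87% for ART retention (70% v 90%).

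**The concern.** Patients within a site all have the same arm, so the information on the arm effect comes from differences between 12 sites. Abstracting 1,200 patients does not change that. The random intercept puts the between-site variance into the standard error, but that variance is itself estimated from about 10 degrees of freedom. Referring the estimate to a normal distribution, or to patient-level degrees of freedom, treats the variance as known. The assurance about standard errors is therefore a property of designs with many clusters, and the article gives it without qualification for a design with 12.

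At stake are the p-values and confidence intervals for all three primary outcomes and for time to ART initiation. The Conclusions section says that favourable findings could support adoption as standard of care in other countries.

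**Working it through.** **Inputs.** From the article: 12 sites; 100 patients per site (all TB/HIV patients) or 32 (measurement cohort); ICC 0.05; two-sided alpha 0.05; the rates above. Assumed: six sites per arm.

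**Step 1: reproduce the stated power.** Design effect = 1 + (m − 1) × 0.05; effective n per arm = 6m / design effect.
- m = 100: 1 + 99 × 0.05 = 5.95; 600 / 5.95 = 100.8 per arm.
- m = 32: 1 + 31 × 0.05 = 2.55; 192 / 2.55 = 75.3 per arm.

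With SE = √{[p₀(1 − p₀) + p₁(1 − p₁)] / n} and λ = 0.20 / SE, normal-reference power is Φ(λ − 1.96). The pooled version uses the pooled variance for the critical value. Power on 10 df is P(T > 2.228), where T is noncentral t with noncentrality λ.

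| Outcome | SE | λ | Normal, pooled / unpooled | Stated | t, 10 df |
|---|---|---|---|---|---|
| ART initiation | 0.0690 | 2.90 | 81.6% / 82.6% | 83% | 74.3% |
| TB treatment success | 0.0593 | 3.37 | 91.3% / 92.1% | 91% | 85.9% |
| ART retention | 0.0631 | 3.17 | 87.4% / 88.7% | 87% | 81.4% |

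The stated figures reproduce within 2 points with a normal reference and lie 5 to 9 points above the t values. The planning made no allowance for cluster degrees of freedom. With 9 df (stratum term) the powers are 73.3%, 85.0% and 80.5%.

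**Step 2: type I error in closed form, normal reference.**
- Variance estimated without bias (REML-type): P(|t₁₀| > 1.96) = 7.8%.
- Maximum likelihood shrinks the variance by 10/12, so the effective cut-off is 1.96 × √(10/12) = 1.789, and P(|t₁₀| > 1.789) = 10.4%.

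**Step 3: simulation under no effect.** There were 3,000 trials per setting. Logistic mixed models were fitted by penalised quasi-likelihood to beta-binomial sites; log-normal frailty models were fitted by penalised likelihood. SAS itself was not run.

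| Setting | REML, z | ML, z | REML, t on site df |
|---|---|---|---|
| ART initiation and TB success, ICC 0.05 | 7.6–7.8% | 10.1–10.4% | 4.8–5.2% |
| Retention, 32 per site, ICC 0.05 | 7.2–7.7% | 9.1–9.9% | 4.2–4.5% |
| Time to ART, frailty variance 0.05–0.2 (assumed) | 7.6–8.2% | 10.2–11.3% | 4.8–5.2% |
| Retention, 32 per site, ICC 0.01 | 4.6% | 5.9% | 2.7% |
| ART initiation, ICC 0.10 | 8.6% | 11.4% | 5.4% |
| ART initiation, unequal sites (two of 300, ten of 60; assumed), ICC 0.05 | 8.0% | 11.0% | 5.1% |
| Same, with stratum term (9 df) | 9.3% | 15.0% | 5.9% |

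**Step 4: interval width.** 2.228 / 1.960 = 1.137, so a t interval on 10 df is about 14% wider than a z interval. On 9 df the ratio is 2.262 / 1.960 = 1.154. Against a maximum-likelihood z interval it is 1.137 × √(12/10) = 1.25.

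**The case against.** The strongest reply is that the faulty test is not in the document. The article names a model class, not a normal reference, a maximum-likelihood fit or patient-level degrees of freedom. The degrees-of-freedom method is an option within the named mixed-model procedure and commonly belongs in an analysis plan, which is not shown here. The same mixed model with REML and t on 10 df runs at about 5%. The sentence on standard errors can be read as saying only that clustering is modelled.

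Much of this stands. A reader might infer that the trial's tests will run at 8–10%, or that a false claim of benefit is twice as likely as stated. The documents do not support either as a flat statement: the reference distribution is open, doubling needs maximum likelihood as well as z, and the inflation nearly vanishes at ICC 0.01 with 32 per clinic. Nor is the model class wrong.

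Two things remain. The article does not merely omit a detail; it asserts that the models as named give appropriate standard errors, and with 12 sites a random intercept does not secure that. And the power figures, which are in the article, carry no allowance for cluster degrees of freedom.

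**Conclusion.** The point holds in conditional form. If the final tests follow the large-sample reference that the power figures imply, type I error at ICC 0.05 and equal site sizes is about 8% (REML-type) to 10% (maximum likelihood) instead of 5%. If they use between-site degrees of freedom, the error is about 5%, but power is about 74%, 86% and 81%. So the stated alpha and the stated powers cannot both hold. The power figures show how the trial was planned; they do not prove how it will be tested.

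The result rests on six sites per arm and, for time to ART initiation, on assumed frailty variances. That outcome is secondary.

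**What to change.** State that inference for the three primary outcomes uses between-site degrees of freedom. Either of these would do:
- the planned mixed model with a REML-type fit and Kenward-Roger or between-within denominator degrees of freedom;
- a t-test on the 12 site summaries, stratified by facility type (9 df).

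For time to ART initiation, use a site-level analysis or a permutation test over the stratified allocation. With one hospital and five health centers per arm (assumed), that gives 2 × 252 = 504 allocations, enough for a test at 5%.

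Qualify the sentence on standard errors so that it refers to the models together with the chosen small-sample method. Restate power on the matching degrees of freedom: about 74%, 86% and 81% on 10 df.

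The change needs wording and an analysis option, and no new data. Its price is intervals at least 14% wider than z-based ones, and lower stated power.
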